## Abstract

**Background:**

Community pharmacies (private retail drug shops or pharmacies) have successfully delivered antiretroviral therapy (ART) to people with human immunodeficiency virus (HIV) and could support integrated tuberculosis (TB) treatment, but the implementation strategies are unclear. To inform a planned pilot randomized trial, we aim to develop person-centered strategies for integrating TB treatment into community pharmacies targeting people with TB/HIV using a Human-Centered Design (HCD) methodology. Here, we describe the study protocol.

**Methods:**

We will employ a three-phased HCD methodology comprising inspiration, ideation, and implementation across six primary health facilities in Kampala, Uganda. Eligible participants will include people with TB/HIV, focal persons for TB and HIV, Ministry of Health officials, and community pharmacy healthcare providers. The inspiration phase will build the themes on barriers and facilitators to integrating TB treatment into community pharmacies from a qualitative study, complemented by participant observations at selected 2–3 community pharmacies to understand the care pathway of people with TB/HIV (journey mapping), including sketching the ideal pharmacy-based TB treatment pick-up. The ideation phase will use design workshops to consolidate identified themes, generate insight statements, including translating them into design opportunities, and conclude with forming low and high-fidelity prototypes. The implementation phase will comprise two rounds of prototype testing, low and high fidelity, with 12–16 participants per round, including people with TB/HIV, focal persons, Ministry of Health officials, and pharmacy health workers. Feedback on usability, desirability, feasibility, and viability will guide iterative refinement, with high-scoring prototypes in system usability surveys prioritized for trial.

**Discussion:**

Through iterative user engagement, we will adapt contextually relevant strategies that will leverage key facilitators and address barriers to TB treatment integration. Strategies demonstrating perceived usefulness, user-friendliness, high acceptability, person-centeredness, and contextual relevance will be adapted and piloted in a planned randomized trial aiming to determine feasibility, acceptability, and fidelity, including preliminary effectiveness.

## Introduction

Tuberculosis (TB) and human immunodeficiency virus (HIV) are the leading causes of morbidity and mortality globally [1]. Optimal treatment outcomes among people with TB/HIV contribute to reducing TB morbidity and mortality, including transmission in the community and ending the TB epidemic [2]. The estimated global treatment success rate among people with TB in 2023 is 88% and around 79% among those with HIV [3]. In sub-Saharan Africa, the rate is 70.1% among people with TB/HIV based on data from a systematic review and meta-analysis [4]. In Uganda, treatment success rates among people with TB/HIV across studies in Uganda range between 54.5% and 74% [5–8]. The World Health Organization (WHO) desired threshold for treatment success rate is ≥ 90%. Therefore, there is a need for innovative approaches to optimize the treatment rates.

In high TB burden settings such as Uganda, missed clinic visits and extended travel distances remain major hindrances to achieving optimal treatment success and adherence among people with TB/HIV. Evidence from a previous Ugandan study showed that people with TB/HIV who travel ≥5 km to a TB clinic have a 17% lower likelihood of achieving treatment success compared to those who travel <5 km [9]. Another study in central Uganda indicated that the mortality rate among people with TB and/or HIV who travel ≥2 km to a TB clinic ranges from 9% to 27% higher when compared with those who travel <2km to the same clinic [10]. Community pharmacies (private retail drug shops or pharmacies) have emerged as innovative and promising platforms for refilling antiretroviral therapy (ART) among people with HIV in Uganda and have registered remarkable viral load suppression and treatment adherence rates. Studies have reported ≥95% ART adherence [11] and ≥95% viral load suppression rates [12] among people with HIV who receive ART refills through community pharmacies. These findings demonstrate community pharmacies as a successful differentiated service delivery model for ART delivery and underscore the potential for integrating TB treatment for people with TB/HIV.

Although community pharmacies show promise for delivering person-centered TB care, several uncertainties remain around the optimal timing of integration, implementation strategies, and real-world effectiveness.

To address these uncertainties and inform the implementation of a planned randomized trial, we designed the Community Pharmacy Tuberculosis Treatment (COPHAT) study, which proposes to use Human-Centered Design (HCD) methodology to adapt person-centered strategies for integrating TB treatment into community pharmacies targeting people with TB/HIV in Kampala, Uganda. Here, we describe the HCD methodology.

HCD offers an innovative, person-centered approach to developing contextually relevant implementation strategies [13]. Through interactive and participatory decision-making among stakeholders [14], HCD aims to improve the acceptability, appropriateness, and feasibility of proposed interventions. Although HCD has been applied to enhance the implementation of interventions for HIV and TB care [15–18], most studies have not published their protocols, which hinders replication and adaptation in other settings. We address this gap by providing a detailed account of our planned application of HCD to TB/HIV intervention design to advance methodological transparency and support the wider adoption of HCD to strengthen person-centered TB/HIV service delivery in high-burden settings.

## Methods and materials

### Study design and setting

We propose to use HCD methodology, a novel, person-centered approach to design thinking, to develop context-relevant implementation strategies [13] and support integration of TB treatment into community pharmacies. HCD methodology supports the generation of meaningful, feasible, and effective solutions to address problems prioritized by stakeholders [13]. The methodology entails an interactive process to achieve shared decision-making by incorporating feedback from stakeholders [14], allowing rapid and iterative co-design and testing of context-relevant strategies before the implementation.

This study will be conducted at all six purposively selected primary healthcare facilities in Kampala, the Capital city of Uganda. The rationale for selecting the facilities is that their HIV clinics are affiliated with some community pharmacies to provide ART refills to stable people with HIV, as part of the Uganda Ministry of Health differentiated service delivery model. Each health facility has a focal person for TB and HIV—a healthcare provider responsible for TB and HIV services delivery, respectively.

The TB clinic is headed by the TB focal person, while the HIV clinic is headed by the HIV focal person. Both focal persons have substantial work experience, training, and knowledge in their respective fields. The clinics provide standardized care per the national treatment guidelines and operate five days a week, with access available during weekends for individuals needing urgent care. The health facilities identify eligible people with HIV who require pharmacy ART refills, assist them in selecting a community pharmacy of their choice, share their unique identifiers with the selected pharmacies, and periodically supply the pharmacies with ARVs for dispensing. In contrast, people with TB/HIV receive anti-TB refills through the TB clinic until treatment completion. These health facilities are described in our previous studies [19–22].

### Study participants and sampling

We will interview all relevant participants (stakeholders), including people with TB/HIV and healthcare providers—TB and HIV focal persons, MoH technical experts, and community pharmacy healthcare providers. The enlisted healthcare providers are engaged in the integration of ART into community pharmacies, so they have a good understanding and experience of the integration processes. The eligible people with TB/HIV will be those aged ≥18 years, have been on both TB and HIV treatment for ≥2 months, and are receiving ART refills either through the community pharmacies or health facilities. The two-month threshold ensures participants have transitioned beyond the initial intensive phase of TB treatment and have adequate exposure to their respective medication refill models, allowing them to provide meaningful insights. We will consecutively sample them across the six TB clinics. During the data collection period, trained research assistants will screen all individuals attending TB/HIV clinic appointments for eligibility, and eligible persons will be provided with study information and invited to participate until the required sample size at each facility is attained. Our sampling approach ensures that all eligible individuals at different stages of their treatment who present to the clinics during the study period are included following informed consent. People with TB/HIV who are acutely ill, require urgent medical care, or are otherwise unable to participate in the interview will be excluded.

Eligible healthcare providers will be those with ≥6 months of work experience in TB management. We will purposively sample TB and HIV focal persons and MoH officials as key informants. For each health facility, we will randomly select one affiliated community pharmacy serving approximately ≥50 people with HIV, and at the selected pharmacy, we will purposively sample 1–2 pharmacy healthcare providers for interviewing.

The pharmacy healthcare providers will be those who have worked in the pharmacy for ≥2 months and are engaged in pharmacy-based ART refills to ensure they have adequate experience and are familiar with the refill process. TB focal persons on leave during the study period and Ministry of Health officials unavailable during data collection will be excluded. Pharmacy personnel not routinely involved in ART refill services, including those temporarily covering shifts, will be excluded.

### Procedures

As shown in Fig 1, the HCD methodology will follow three distinct phases: inspiration, ideation, and implementation [23]. This process is conceptually grounded in the Double Diamond model of design, which emphasizes iterative cycles of divergence and convergence to structure problem exploration and solution development [24]. Fig 1. Human-Centered Design (HCD) methodology phases for adapting implementation strategies to integrate TB treatment into community pharmacies for people with TB/HIV in Kampala, Uganda.

**Fig 1 pone.0344913.g001:**
[figure not shown]
Human-Centered Design (HCD) methodology phases for adapting implementation strategies to integrate TB treatment into community pharmacies for people with TB/HIV in Kampala, Uganda. The diagram illustrates the three sequential stages of the methodology, along with the corresponding main activities.

The inspiration phase aligns with the “Discover” and “Define” stages of the Double Diamond, where insights from qualitative data are explored broadly (divergence) and then synthesized into priority themes and insight statements (convergence). The ideation phase corresponds to the “Develop” stage, characterized by generating and refining potential solutions through iterative expansion and narrowing of design options. The implementation phase aligns with the “Deliver” stage, focusing on testing, refining, and operationalizing selected strategies within real-world pharmacy settings.

### Phase 1: Inspiration phase (qualitative work—interviews and observations)

The inspiration phase will build on our prior qualitative work that identified barriers and facilitators to integrating TB treatment into community pharmacies [25]. Two reviewers (JI and AS) will independently review and select themes on identified barriers and facilitators to integrating TB treatment into community pharmacies, which will be reviewed and approved by a third senior reviewer (AC). Once consensus has been established regarding the key themes amongst the reviewers (JI, AS, and AC), we will generate insight statements from the themes to capture user perspectives, motivations, and tensions, allowing us to define specific human needs.

The generation of insight statements is specific to HCD methodology and is an academically novel approach to assigning meaning to themes. The three reviewers (JI, AS, and AC) will review, discuss, and refine the insight statements until consensus is reached. Building on the insight statements, we will develop design opportunities—propose actionable solutions to identified challenges and develop low-fidelity prototypes for refinement during the subsequent phases of the HCD methodology. The low-fidelity prototypes will also be reviewed, discussed, and refined until consensus is reached. Besides the existing qualitative work, we will conduct observations across 2–3 community pharmacies to understand the care pathway of people with TB/HIV (journey mapping) and sketch the ideal pharmacy-based TB treatment pick-up. The observations will be conducted using a checklist and will focus on five areas: 1) activities: tasks performed, duration, and sequence; 2) the environment: physical characteristics of the pharmacy, functioning and use; 3) interactions: person-to-person and person-to-object engagements; 4) objects: types of objects and their characteristics, including the relation to people and activities, and 5) users: presence, behaviors, roles, and relationships.

### Phase 2: Ideation phase: brainstorming and prototype development

In this phase, we will engage the participants, namely people with TB/HIV, focal persons for HIV and TB, MoH technical experts, and community pharmacy healthcare providers in a design workshop comprising 8–12 people. We will present the identified themes, insight statements, and design opportunities from the inspiration phase using a PowerPoint format to facilitate consolidation. The participants will vote to select 3–4 insights related to challenges they wish to be addressed immediately, and another 3–4 insights for future action. Voting will be conducted privately using individual ballots, and selections will be tabulated by the research team without disclosing individual choices to ensure the process is independent and unbiased. Thereafter, participants will be organized into smaller groups of 3–5 people for brainstorming sessions focused on the selected insights, guided by a *priori* defined 2–3 *“How Might We”* (HMW) questions to generate solutions or prototypes. The brainstorming session will aim to overcome cognitive fixedness—a mindset where one consciously or unconsciously assumes only a one-way approach to a situation. We propose conducting 2–3 brainstorming sessions with 5–10 people with TB/HIV aged ≥18 years, 3–5 focal persons for TB, 3–5 focal persons for HIV, and 3–4 Ministry of Health officials.

Anticipated prototypes may include guideline or standard operating procedure development to support TB treatment integration, multi-month dispensing of TB medications, medication side effect assessment using pre-defined questions, a new pathway for medication pick-ups, and laboratory-only sputum smear follow-up testing, among others. To prioritize and select the prototypes, we will use an impact-effort matrix for plotting ideas based on their perceived impact (low vs. high) and implementation effort (low vs. high). We will select ideas in the high-impact, low-effort quadrant for testing. The identified prototypes will be packaged for iterative testing and refinement in the subsequent phase. To accommodate the participants’ competing responsibilities, the ideation phase may be held off-site at the Makerere University Infectious Diseases Institute boardroom, including weekends. Where feasible, it will be conducted at the health facilities.

### Phase 3: Implementation phase: prototype testing, iteration, and refinement

We will conduct two rounds of prototype testing, low and high fidelity, each involving 12–16 participants deemed sufficient to attain thematic saturation, including people with TB/HIV, TB and HIV focal persons, MoH officials, and pharmacy health workers. In the low-fidelity phase, participants will engage in 60-minute individual interviews with a talk-aloud session to review the prototype, discuss what works, and provide feedback on desirability, feasibility, and viability using a 5-point Likert scale, ranging from a low to high score (1 = Very low, 2 = Low, 3 = Moderate, 4 = High, and 5 = Very high). The participants will also compare 2–3 prototype options and vote for their preferred version. Findings from this phase will guide revisions before the high-fidelity phase, during which usability will additionally be assessed using the System Usability Scale (SUS) using a simple, 10-item standardized questionnaire [26]. Each SUS question will be ranked on a 1–5 scale, with the lowest score indicating a strong disagreement with the prototype and the highest score suggesting otherwise. We will implement the SUS until a higher level of acceptability, defined as a median score of >80.3, is reached [26]. A maximum of three iterative refinement cycles will be conducted to allow systematic improvement of prototypes based on user feedback. Prototypes achieving higher SUS and Likert-scale scores will be prioritized for pilot implementation in a hybrid effectiveness–implementation randomized trial at two public primary healthcare facilities in Kampala, Uganda.

If the predefined SUS threshold of >80.3 is not achieved after the maximum number of iterations, the prototype with the highest median SUS score (provided it meets or exceeds the acceptable usability benchmark of ≥68) and demonstrates consistent improvement across rounds will be selected. Qualitative user feedback and feasibility considerations will additionally inform the final selection to ensure contextual appropriateness. This iterative, user-centered approach ensures systematic refinement and selection of the most acceptable, feasible, and effective intervention prototypes.

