### Statistical methods: Sample size and data analysis

The sample sizes for the different phases of the HCD methodology have been described above. However, the exact sample sizes will depend on thematic saturation, a point at which no new information emerges even when additional data are collected. All interviews will be audio-recorded and professionally transcribed verbatim by experienced qualitative researchers. The transcripts will be checked for accuracy by replaying and listening to the audio recordings, and any inconsistencies will be identified and corrected.

The corrected transcripts will be uploaded into NVivo software for thematic analysis using an inductive approach. To minimize subjective bias, two independent analysts (JI and AS) will conduct the analysis. Each analyst will independently and repeatedly read a few of the transcripts to achieve familiarity with the data (data immersion), identify recurring and significant patterns, and develop codes. Through consensus, the analysts will develop an initial codebook based on the independent codes, which will be used to code the remaining transcripts and remain open to newer codes. We will iteratively refine and group the codes into categories and subsequently into themes, and present them alongside illustrative quotes to support interpretation. Reporting of the qualitative findings will adhere to the Standards for Reporting Qualitative Research (SRQR) guidelines [27].

In SUS data analysis, we will normalize the data by subtracting 1 from each odd-numbered question (questions 1, 3, 5, 7, and 9) and 5 from each even-numbered question (questions 2, 4, 6, 8, and 10). This process will create new values, which will be summed to produce a total score, which will be multiplied by 2.5 to yield scores that will range from 0 to 100, with 68 as the average score [26]. We will categorize the SUS scores as ≤50, 51–68, 68–80.3, and more than 80.3 to suggest unacceptable, poor, good, and excellent strategies/prototypes, respectively [28]. Prototypes with SUS scores ≥68 will be considered usable and may be tested in the planned trial.

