Despite the strengths of HCD methodology, there are certain limitations. The methodology can be time- and resource-intensive, requiring skilled facilitation and multiple engagement rounds, which may be challenging. To mitigate this limitation, we will use experienced and skilled individuals with expertise and training in the methodology. Additionally, most HCD-generated solutions/prototypes are often context-specific and may limit generalizability. There is also the risk of incomplete representation of participant engagement, although our proposed multi-level participant engagement approach will likely mitigate this limitation. In addition to subjective bias during data analysis, the HCD process may be affected by selection bias, as participants attending workshops may differ from those who do not; social desirability bias, where participants provide responses they perceive as favorable; and facilitation or group influence bias, where dominant voices may shape group decisions. To minimize these biases, we will use purposive and consecutive sampling, conduct confidential and independent voting, and employ trained facilitators to ensure equitable participation and capture diverse perspectives. Finally, the methodology is effective at generating user-centered solutions but may not fully address structural or system-level barriers. To mitigate this limitation, we will combine the HCD methodology with CFIR to ensure both user-centeredness and methodological rigor, while enhancing the potential for scalability and sustainability of resulting implementation strategies.

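### The measures listed against social desirability bias do not act on individual prototype ratings, and the low-fidelity Likert scores are given in a recorded one-to-one interview

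*Protocol article*

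**What the plan says.** All references are to the protocol article.

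- **Study strengths and limitations.** Social desirability bias is listed among the biases that may affect the process. The measures offered against the listed biases are the sampling approach and a promise to "conduct confidential and independent voting, and employ trained facilitators", the facilitators being there to secure balanced participation. No phase is named for the confidential voting.
- **Phase 2 (ideation).** Workshop participants vote on which insights to tackle now and which later. Here the procedure is spelled out: "Voting will be conducted privately using individual ballots, and selections will be tabulated by the research team without disclosing individual choices".
- **Phase 3 (implementation), low-fidelity round.** The plan states: "participants will engage in 60-minute individual interviews with a talk-aloud session to review the prototype, discuss what works, and provide feedback on desirability". Two further aspects, viability and feasibility, are rated as well, all three on a five-point scale. Then: "The participants will also compare 2–3 prototype options and vote for their preferred version". How this vote is cast is not said. "Findings from this phase will guide revisions before the high-fidelity phase".
- **Phase 3, high-fidelity round.** Here "usability will additionally be assessed using the System Usability Scale (SUS) using a simple, 10-item standardized questionnaire". Whether it is self-completed or administered by an interviewer is not said. Refinement continues until the median SUS exceeds 80.3, with at most three cycles. If that is never reached, the prototype with the highest median may still be chosen if it reaches 68 and has improved consistently. Prototypes with higher SUS and Likert scores are prioritised for the trial. Qualitative feedback and feasibility also inform the final choice.
- **Statistical methods.** "All interviews will be audio-recorded". Prototypes with a SUS of 68 or more count as usable and may enter the planned trial.

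**The concern.** The authors recognise that participants may give answers they think are welcome. They protect the early, less consequential choice (which insights to work on) with a private ballot. The later ratings, which help decide what goes into the trial, have no comparable protection in the text.

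A participant who has just talked through a prototype with a member of the study team, on tape, and then rates it is in the setting where courtesy is most likely to lift the score. On a five-point scale this does two things. It raises the level, and it pushes ratings towards the top category, so that a better and a weaker prototype become harder to tell apart. If the SUS were collected in the same setting, there would be a further consequence, because the SUS is judged against fixed cut-offs. An upward drift could end refinement before usability has really reached the target.

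**Working it through.** The plan gives no figure to reproduce on this point. The check is to trace each input to the decision back to its stated way of collection, and then to see how sensitive the cut-offs are.

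**Step 1. Inputs set side by side.**

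| Input | Stated way of collection | Use | Safeguard against courtesy answers |
|---|---|---|---|
| Vote on insights (Phase 2) | Private ballot | Chooses the insights to address | Described |
| Likert ratings (Phase 3, low fidelity) | Within an individual, audio-recorded talk-aloud interview | Named criterion for the trial | None described |
| Preferred-version vote (Phase 3, low fidelity) | Not stated | Guides revisions | Possibly the general promise of confidential voting |
| SUS (Phase 3, high fidelity) | Questionnaire, mode not stated | Stopping rule (above 80.3), fallback (at least 68), named criterion for the trial | None described |

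**Step 2. Do the listed measures reach the ratings?** Sampling decides who takes part. Facilitators, as described, keep dominant voices in check in groups. Confidential voting protects votes. A rating given in a one-to-one interview is not a vote, even if the promise is read as covering every phase. So the Likert ratings are left uncovered on any reading.

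**Step 3. Effect on the Likert scores.** There is no cut-off on this scale, so only comparisons between prototypes matter. If two prototypes would honestly be rated 3 and 4, adding one step to both gives 4 and 5, and the order holds. If they would be rated 4 and 5, adding one step gives 5 and 5 because the scale stops there, and the difference is lost. These ratings are illustrative.

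**Step 4. Sensitivity of the SUS cut-offs, if the SUS is collected in the same setting.** The stated range of 0 to 100 with a multiplier of 2.5 implies 100 / 2.5 = 40 raw points over ten items, that is 0 to 4 per item (standard scoring).

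- One favourable step on one item: 1 × 2.5 = 2.5 points. On three items: 7.5. On five items: 12.5.
- Distance between the cut-offs: 80.3 − 68 = 12.3 points; 12.3 / 2.5 = 4.92 raw points; 4.92 / 10 = 0.49 of a step per item.
- From a true median of 70, these shifts give 72.5, 77.5 and 82.5. Only the last exceeds 80.3. Since 70 already meets 68, the consequence would be earlier stopping; an unusable prototype would not have been let in.

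**Step 5. Illustration of early stopping.** Assumptions that are not in the documents: normal scores with SD 12.5, rounded to 2.5; no real improvement between cycles; independent cycles. Simulated probability that the median exceeds 80.3 in one cycle, at the plan's 12 and 16 participants:

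| True mean | n | No shift | +2.5 | +5 | +10 |
|---|---|---|---|---|---|
| 75 | 12 | 0.09 | 0.23 | 0.44 | 0.85 |
| 75 | 16 | 0.07 | 0.20 | 0.43 | 0.87 |
| 70 | 12 | 0.006 | 0.03 | 0.10 | 0.44 |
| 70 | 16 | 0.002 | 0.015 | 0.07 | 0.43 |

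Over up to three cycles, 1 − (1 − p)³ at a true mean of 75 and n = 12 gives 1 − (1 − 0.093)³ = 0.25 with no shift and 1 − (1 − 0.438)³ = 0.82 at +5.

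**The case against.** A sponsor could fairly say the following.

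- The promise of confidential voting is made for the process as a whole, so it may well cover the Phase 3 vote. This stands. A reader might infer that private ballots apply only to ideation, but the text does not say so; it merely describes the ballot there and nowhere else.
- Nothing says that the preferred-version vote is given to an interviewer, and that vote guides revisions; it is not a named criterion for the trial. Both points stand.
- The interview setting and the cut-offs belong to different instruments. The interview is documented for the low-fidelity Likert ratings, which have no cut-off. The cut-offs belong to the SUS, whose mode of administration is unstated. This stands, and it is the most important limit on the point.
- Who completes a ten-item form, and how, is detail that an article may leave to a fuller protocol or interview guide. This also stands: silence on the SUS mode is not in itself a fault.
- A shift shared by all prototypes leaves their order unchanged, and qualitative feedback and feasibility also inform the final choice. This stands, apart from the ties that the top of the scale can produce.
- The bias is disclosed, the plan claims only to reduce it, and raters include health workers and officials as well as patients. This stands, but disclosure does not make the listed measures reach the ratings.

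None of this answers the core: the bias is named, and no listed measure acts on individual ratings that the text itself places in a recorded interview.

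**Conclusion.** The point holds in a limited form. The stated mitigation does not cover individual ratings, and the Likert scores that the plan describes, which count in choosing prototypes, are given within a recorded one-to-one interview. The likely effect is inflated ratings and weaker discrimination between prototypes. Its size cannot be worked out from the documents.

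The effect on the SUS cut-offs is conditional on the SUS being collected in the same way. If it is, about half a step per item spans the distance from 68 to 80.3. Under the assumptions shown, a drift of 5 points from a true mean of 75 raises the chance of stopping in one cycle at n = 12 from 0.09 to 0.44.

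A reader might go further and infer that all the scores choosing the trial strategy are spoken to an interviewer, so that the 68 and 80.3 decisions are already biased upwards. The documents do not support that: they place only the Likert ratings in the interview. This is a worthwhile, inexpensive improvement and does not threaten the study's validity.

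**What to change.** In the Phase 3 section, state that participants complete the Likert items, the preferred-version vote and the SUS privately on a coded form, after reviewing the prototype and before discussing their ratings. For participants who cannot read (the ethics statement allows thumbprint consent), read the standard items aloud while the answer is marked out of the interviewer's sight, leaving the SUS items unchanged. Tabulate the forms as in Phase 2, without disclosing individual answers. The talk-aloud discussion stays face to face. Then reword the limitations section so that its mitigation covers ratings as well as votes and says which phases it applies to.

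The cost is one short form and a change in the order of the session, with no extra staff or participants. There are two drawbacks. Individual ratings can be probed less directly in the interview, although the code still links them to the transcript at analysis. Privacy is also only partial for those who need the items read aloud.
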